## Abstract

**Background:**

There are wide variations in maternal-newborn care practices and outcomes across Ontario. To help institutions and care providers learn about their own performance, the Better Outcomes Registry & Network (BORN) Ontario has implemented an audit and feedback system, the Maternal-Newborn Dashboard (MND), for all hospitals providing maternal-newborn care. The dashboard provides (1) near real-time feedback, with site-specific and peer comparison data about six key performance indicators; (2) a visual display of evidence-practice gaps related to the indicators; and (3) benchmarks to provide direction for practice change. This study aims to evaluate the effects of the dashboard, dashboard attributes, contextual factors, and facilitation/support needs that influence the use of this audit and feedback system to improve performance. The objectives of this study are to (1) evaluate the effect of implementing the dashboard across Ontario; (2) explore factors that potentially explain differences in the use of the MND among hospitals; (3) measure factors potentially associated with differential effectiveness of the MND; and (4) identify factors that predict differences in hospital performance.

**Methods/design:**

A mixed methods design includes (1) an interrupted time series analysis to evaluate the effect of the intervention on six indicators, (2) key informant interviews with a purposeful sample of directors/managers from up to 20 maternal-newborn care hospitals to explore factors that influence the use of the dashboard, (3) a provincial survey of obstetrical directors/managers from all maternal-newborn hospitals in the province to measure factors that influence the use of the dashboard, and (4) a multivariable generalized linear mixed effects regression analysis of the indicators at each hospital to quantitatively evaluate the change in practice following implementation of the dashboard and to identify factors most predictive of use.

**Discussion:**

Study results will provide essential data to develop knowledge translation strategies for facilitating practice change, which can be further evaluated through a future cluster randomized trial.

## Background

Pregnancy, labor, birth, and the early postpartum period are characterized by high utilization of health-care services, and outcomes from this period have important implications for current and future population health. There are approximately 140,000 babies born in Ontario hospitals each year [1]. Wide variation in maternal-newborn care practices and outcomes exists across Ontario indicating that optimal care is not always delivered and there are opportunities to address quality of care (see Fig. 1). To help institutions and care providers learn more about their own performance, the Better Outcomes Registry & Network (BORN) Ontario implemented the Maternal-Newborn Dashboard (MND) [2], an audit and feedback (A&F) system for all maternal-newborn hospitals in Ontario.

**Fig. 1 Fig1:**
[figure not shown]
Examples of practice variation across Ontario for selected indicators

BORN Ontario is a prescribed registry under Ontario Personal Health Information Protection Act (PHIPA) privacy legislation and is able to collect, disclose, and use personal health information for the purpose of improving care and patient outcomes. The BORN Information System (BIS), an Internet-based data collection system, is operational in all hospitals providing maternal-newborn care and has data for all hospital births. Maternal demographics and health behaviors, pre-existing maternal health problems, obstetric complications, intrapartum interventions, and birth and newborn outcomes are captured at the time of birth from medical records, clinical forms, and patient interviews. These data are either entered into the BIS by hospital staff or uploaded directly from hospitals’ electronic health records. Each site has access to their own data, and BORN Ontario reports on outcomes aggregated at the provincial level at regular intervals [1]. An ongoing data validation process [3], quality checks, and formal training sessions for individuals entering data assure a high level of data quality (see Fig. 2). A number of papers have been published using these data [1, 4–6].

**Fig. 2 Fig2:**
[figure not shown]
BORN data entry and validation process flow chart for hospital birth data

The MND is an A&F reporting tool within the BIS and was launched in November 2012. The MND targets six key performance indicators (KPIs), which were identified during the rigorous development process [2] (see Table 1).

**Table 1 Tab1:** BORN maternal-newborn dashboard key performance indicators, definitions, and benchmarks

Key performance indicators	Target (green)	Warning (yellow)	Alert (red)	Definitions
	%	%	%	
1. Proportion of newborn screening samples that are unsatisfactory for testing	<2.0	2.0–3.0	>3.0	Number of newborn screening samples with unsatisfactory reason(s), expressed as a percentage of the total number of newborn screening samples submitted from a given hospital/midwifery practice. NOTE: Samples coded as unsatisfactory only due to collection at less than 24 h of age (i.e., there are no other reasons the sample has been deemed unsatisfactory) will not be considered as unsatisfactory for this analysis, since sample collection at less than 24 h of age is recommended in cases of early discharge, transfer, or transfusion.
2. Proportion of episiotomy in spontaneous vaginal births	<13.0	13.0–17.0	>17.0	Number of women having a spontaneous vaginal birth who have an episiotomy expressed as a percentage of the total number of women having a spontaneous vaginal birth (in a given place and time).
3. Proportion of formula supplementation in term infants whose mothers intended to breastfeed	<20.0	20.0–25.0	>25.0	Number of term live babies receiving formula supplementation expressed as a percentage of the total number of term babies whose mothers intended to breastfeed (in a given place and time).

For A&F to be effective, it must be timely, individualized, non-punitive, customizable, and perceived as relevant and credible [7–9]. A rigorous development process was undertaken to ensure credibility of the BORN Ontario MND [2]. First, the framework for selecting core quality measures (clinically meaningful, feasible to monitor, and actionable/amenable to change) was used to guide selection of the KPIs for the MND and allowed us to identify a manageable number of indicators [2]. We then validated the six potential indicators as appropriate for use across the province by assessing current performance of these indicators across the 14 health regions in Ontario. Simultaneously, evidence summaries for each of the potential indicators were developed in collaboration with the Knowledge to Action Research Centre at the Ottawa Hospital Research Institute [10–14] (http://bornontario.ca/en/born-information-system/report-training/). To establish benchmarks for the KPIs, we used a combination of peer-reviewed literature, current clinical practice within Ontario, and recommendations from clinical experts. Glantz’s recommendation to accept lower intervention rates if higher rates do not improve outcomes was a guiding principle [15], as well as other risk assessment techniques such as restricting patient populations to more homogeneous subgroups.

The BORN MND report provides users with (1) near real-time feedback, site-specific, and peer comparison data for the aforementioned six KPIs; (2) a signal or visual display of evidence-practice gaps related to the KPIs; and (3) benchmarks to provide direction for practice change (see Fig. 3). The ultimate goal is to promote evidence-informed practice, decrease variability in care processes related to the selected KPIs, and improve maternal-newborn outcomes.

**Fig. 3 Fig3:**
[figure not shown]
BORN maternal-newborn dashboard sample home page

Awareness of practice issues and agreement about the evidence and need for change are essential first steps for adoption of new care practices [16]. This suggests that increasing practitioner awareness about a problem (e.g., by providing feedback about KPI rates) will facilitate engagement in practice change, reduce practice variation, and lead to improved patient care. In 2010, we conducted a pilot project in one health region in Ontario to evaluate the effectiveness of the A&F process using an early version of the MND [4]. This feasibility study proved successful in reducing the rate of elective repeat Caesarian section < 39 weeks' gestation in the region and suggested that the MND may be a useful tool to facilitate practice change across the province [4].

With the implementation of the new MND system, BORN Ontario is in a unique position to evaluate this A&F tool. Dashboards have been used for a variety of purposes within health care but are primarily implemented to drive quality improvement. The use of a dashboard may improve quality of care and patient outcomes [17–20]. A Cochrane review of 140 randomized controlled trials demonstrated small but important changes in practice [9], and the universal use of a maternity dashboard has been strongly recommended in the UK to improve clinical practice [21]. However, it is unclear why performance improves in some settings and not in others, what resources are needed to increase the effectiveness of a system like the MND, and which attributes of electronic A&F have the greatest effect. We plan to address this issue by evaluating the effect of the MND among hospitals in Ontario to facilitate practice change for selected KPIs for maternal-newborn care and explore factors predicting variation in response.

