#### Analysis

The data to support the primary ITS analysis will come from the BIS. The MND implementation occurred from November 2012 to March 2013, allowing time for all hospitals to gain experience with data entry and use of the dashboard. MND data for the 3-year pre-implementation period (November 2009–October 2012) and the 2-year post-implementation period (April 2013–March 2015) will be available after April 2016. Thus, each site will contribute 3 years of data to the pre-implementation phase and 2 years after implementation. We will exclude data from the 5–6 months between the pre- and post-implementation phases from the analysis. For our primary ITS analyses, the six KPIs will be expressed as monthly proportions after pooling across all hospitals. Pooling is necessary to allow inclusion of low birth volume hospitals and to accommodate all six KPIs, including two that assess performance of uncommon outcomes. Time series plots will be used to visually inspect the immediate and long-term effect of the intervention and the presence of trends, cyclical patterns, and outliers. A segmented regression analysis will be completed using separate intercepts and slopes for the time periods before and after implementation of the MND [26, 31]. The presence of autocorrelation will be assessed using Durbin-Watson tests, as well as visual inspection of residual plots. If autocorrelation is present, an autocorrelation parameter will be included in the model. The results of the segmented regression analysis of each KPI will be reported as level and trend changes after the intervention, with 95 % confidence intervals (CI). All analyses will be conducted using SAS v. 9.4.

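### For KPI 4, the pre-implementation series pools in a health region that had an early version of the dashboard in 2010, so the baseline trend and estimated effect can be biased, in a direction the documents do not settle

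*Protocol article*

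**What the plan says.** The Background of the protocol article describes a pilot: "In 2010, we conducted a pilot project in one health region in Ontario to evaluate the effectiveness of the A&F process", carried out "using an early version of the MND". It gives the result as follows: "This feasibility study proved successful in reducing the rate of elective repeat Caesarian section" before 39 weeks in that region. Table 1 defines KPI 4 as repeat caesarean before 39 weeks in low-risk women at term, so the pilot outcome is in substance a study outcome.

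Objective 1, Analysis, sets the windows as "3-year pre-implementation period (November 2009–October 2012) and the 2-year post-implementation period (April 2013–March 2015" and states that "each site will contribute 3 years of data to the pre-implementation phase and 2 years after implementation". On pooling it says "the six KPIs will be expressed as monthly proportions after pooling across all hospitals". On the model it says "A segmented regression analysis will be completed using separate intercepts and slopes for the time periods before and after implementation of the MND". The sample size section confirms 94 hospitals, 60 time points and four coefficients.

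No section removes the pilot region, dates its exposure separately or lists it as a limitation. Objective 4 leaves hospitals out only for low birth volume or because they did not answer the survey.

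**The concern.** A segmented regression measures the intervention effect against the baseline trend carried forward. If some baseline hospitals had already changed because of a forerunner of the same intervention, that trend partly reflects the intervention. The level and trend changes for KPI 4 are then measured against the wrong line.

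The planned checks in Objective 1, Methods, do not deal with this. Outcomes the dashboard does not target cannot reveal an earlier dashboard effect on KPI 4. The control provinces are meant to share Ontario's pre-implementation trend, and that is the trend the pilot may have altered.

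Objective 4 uses individual hospital data, so any pilot effect in a participating pilot hospital is not diluted by the rest of the province. It could distort that hospital's estimated response and the survey factors associated with it.

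**Working it through.** **The plan's own count.** November 2009 to October 2012 is 36 months and April 2013 to March 2015 is 24. The total is 36 + 24 = 60, as stated. The ten-per-coefficient rule needs 10 × 4 = 40, which is met. The whole of 2010 lies inside the baseline.

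**Set-up.** Number the months with November 2009 = 1 and October 2012 = 36. Months 37–41 are excluded. April 2013 = 42 and March 2015 = 65. The model is intercept, time, level change at month 42 and trend change after it, fitted by ordinary least squares. Let *s* be the pilot region's share of the KPI 4 denominator and *D* its fall in percentage points. The pilot adds −*sD* to the pooled series while its effect lasts. The documents give neither *s*, *D*, the start month nor the persistence; all four are assumptions here. Improvement on KPI 4 is a fall, so a positive bias means the benefit is understated.

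**One case by hand: lasting fall from June 2010 (month 8), *sD* = 1.** There are 7 baseline months before onset and 29 after.
- Baseline slope = −(7 × 29 / 2) / [36 × (36² − 1) / 12] = −101.5 / 3885 = −0.0261 per month.
- Baseline mean = −29/36 = −0.806, centred at month 18.5.
- Projection to month 42: −0.806 − 0.0261 × 23.5 = −1.420. The actual value is −1, so the level bias is +0.42.
- Projection to month 65: −0.806 − 0.0261 × 46.5 = −2.020. The actual value is −1, so the March 2015 bias is +1.02.

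**Bias per pooled point (*sD* = 1), from the same fit:**

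| Pilot effect | Start (2010) | Level change | Effect at March 2015 |
|---|---|---|---|
| Lasting | January | +0.150 | +0.351 |
| Lasting | June | +0.420 | +1.020 |
| Lasting | December | +0.543 | +1.428 |
| Gone after 12 months | January | −0.393 | −1.103 |
| Gone after 12 months | June | −0.030 | −0.385 |
| Gone after 12 months | December | +0.406 | +0.477 |
| Fading over 24 months | January | −0.245 | −0.825 |
| Fading over 24 months | June | +0.133 | −0.077 |
| Fading over 24 months | December | +0.581 | +0.811 |

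**Scaling.** The Background mentions 14 health regions; an equal share is *s* = 1/14. With *D* = 10, *sD* = 0.714.
- Lasting fall: level bias 0.714 × (0.150 to 0.543) = +0.11 to +0.39; March 2015 bias 0.714 × (0.351 to 1.428) = +0.25 to +1.02.
- Fall gone after 12 months: March 2015 bias 0.714 × (−1.103 to +0.477) = −0.79 to +0.34.
- Upper end for a lasting fall at the same share: *D* = 30 gives a level bias of up to +1.16 and a March 2015 bias of up to +3.06.
- A share of 0.20 with *D* = 30 gives up to +3.26 and +8.57.

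**Sampling error for comparison.** Take the stated denominator of about 200 a month, an assumed KPI 4 rate of 15% to 50%, binomial variation and no autocorrelation. The SE is about 1.4 to 2.0 points for the level change and 2.2 to 3.0 points for the March 2015 effect.

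**The case against.** The strongest reply is that the article reports a pilot effect on one outcome in one region. Nothing connects the pilot with the other five KPIs. A reader might infer that the whole evaluation is contaminated; the text does not support that, and the point is limited to KPI 4.

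A reader might also infer that the pilot hospitals were exposed for most of the baseline and that the bias runs towards no benefit. The article says only that the pilot took place in 2010. It gives no start month, length or persistence. The table shows that a short-lived early fall reverses the sign, so neither inference can be drawn. Nor can it be said that pilot hospitals will look like non-responders in Objective 4. That needs a lasting fall and little further response, and with about 50 responding hospitals expected it is unknown how many pilot hospitals would enter.

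At an equal share and a 10-point fall the bias is well under one SE. That stands as a limit on severity. It does not dispose of the point, because this bias is systematic and sampling error is not.

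Finally, the article is a condensed document, and sensitivity analyses are often left to a fuller plan. That has some weight. But the article itself fixes the window, the sites, the pooling and the single interruption, and these do not fit its own account of the pilot. Inspecting time series plots and acknowledging other causes of change in general terms do not resolve it.

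**Conclusion.** The point holds for KPI 4 only. By the article's own account, one region had an early form of the intervention, with a reported effect on this outcome, inside the period the model treats as unexposed. The KPI 4 pre-trend and the estimated level and trend changes can therefore be biased.

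Direction and size cannot be determined from the documents. The bias is modest at an equal regional share and a 10-point fall. It reaches the size of the March 2015 SE only with a large lasting fall, a large share or both. This is a moderate weakness that calls for a prespecified check; it does not invalidate the ITS.

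A reader might conclude that the pilot region should be dropped from the primary analysis. The stated objective is the population effect across Ontario, and those hospitals also received the new dashboard. Dropping them would change the question being answered.

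**What to change.** Keep all 94 hospitals as the primary Ontario-wide analysis. For KPI 4, prespecify a second ITS analysis, and a matching Objective 4 model, that either excludes the pilot region's hospitals or gives them their own 2010 exposure term. Report both, interpret the KPI 4 effect in light of the difference, and name the earlier exposure among the limitations.

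The cost is small, since the investigators ran the pilot and should be able to identify the hospitals. With an assumed equal share, exclusion takes the monthly denominator from about 200 to 200 × 13/14 ≈ 186, still above the 100 the plan cites, and keeps all 60 time points. Standard errors in that analysis grow by a factor of √(14/13) ≈ 1.04, about 4%.

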### Goal and objectives

The overall goals of this mixed methods study are to increase our knowledge of how A&F works in hospital settings and to support the design of cluster randomized trials according to the Medical Research Council-recommended framework for evaluation of complex interventions [22].

More specifically, the study aims to:Conduct an interrupted time series (ITS) analysis to evaluate the population effect of implementing the MND across Ontario by comparing hospital performance on six selected KPIsQualitatively explore factors that potentially explain differences in the use of the MND among hospitals by conducting key informant interviews with directors/managers from a diverse group of maternal-newborn hospitals in OntarioMeasure factors potentially associated with differential effectiveness of the MND by developing and implementing a survey of all maternal-newborn hospitals in OntarioIdentify factors significantly associated with differences in hospital performance before and after implementation of the MND by conducting a longitudinal multivariable regression analysis of six KPIs

## Methods/design

### Design

This mixed methods study will use quantitative (objectives 1, 3, and 4) and qualitative (objective 2) methodologies to address the research objectives. We will implement a sequential exploratory design by using the qualitative findings (from interviews) to inform the quantitative components of the study (survey and regression analysis) [23].

### Theoretical framework

The Promoting Action on Research Implementation in Health Services (PARiHS) [24] framework will guide this study. The PARiHS framework contends that *evidence*, *context*, and *facilitation* are the key influencing factors for successful implementation of a new innovation for practice change. The most successful implementation occurs when evidence is scientifically robust and matches professional consensus and patient preferences (high evidence), when the context is receptive for change with sympathetic cultures, strong leadership, and appropriate monitoring and feedback systems (high context), and when there is appropriate facilitation of change, with input from skilled external and internal facilitators (high facilitation) [24]. Based on this framework, we hypothesize that successful adoption of the MND (a new innovation) to facilitate practice change will be dependent upon the nature and the clarity of the evidence on which it is based, the quality of the context (environment) in which it is being implemented, and the type of facilitation needed to ensure successful adoption. Concepts from the PARiHS framework will inform development of our semi-structured interview guide and the provincial survey for this study.

A description of the methods for each of the objectives is presented below.

### Objective 1—to evaluate the population effect of implementing the MND across Ontario

#### Methods

An ITS analysis of six KPIs (Table 1) will be used. This quasi-experimental design can be used to determine the effect of a complex intervention introduced at a specific point in time [25]. It is superior to many other quasi-experimental and observational designs, such as before and after designs, in that it avoids threats to internal validity such as history and maturation [26, 27]. By using outcomes assessed at multiple time points, it allows the estimation of an underlying secular trend prior to the intervention. The estimated intercept and trend before and after the intervention can then be compared to determine both the immediate and long-term effects of the intervention. While ITS designs are useful for determining whether an intervention has had an effect on the outcome while accounting for any underlying secular trend, the possibility of confounding by temporally concurrent interventions still poses an important threat to the internal validity of this design [28]. We will use two approaches to assess “possible rival explanations” for any apparent effect of the MND [29]. First, we will assess two non-equivalent outcomes measured in the same population over the same period of time: CS rates in nulliparous women with induced labor and the proportion of low-risk women at term gestation having electronic fetal monitoring in labor. Since these outcomes should not be affected by the MND, a finding of no change in these variables will strengthen our ability to attribute any change in the KPIs to the MND. Second, we will use data from two Canadian provinces (Nova Scotia and British Columbia) as a non-equivalent control group. A suitable control group must have similar baseline characteristics and pre-implementation temporal trends, except for the MND intervention [30].

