#### Sample size considerations

The ITS analysis will include monthly data aggregated from 94 hospitals over 5 years (60 time points total). Recommendations are to include between 40 and 50 observations for robust statistical analysis of ITS designs [32]; moreover, to avoid over-fitting of segmented regression models, at least 10 observations for each regression coefficient is required [33]. With 4 regression coefficients in our planned analyses, 60 time points is adequate. Furthermore, to help ensure stability of the monthly proportions, it is recommended that measurements be based on at least 100 observations at each time point. After pooling across all hospitals (approximately 12,000 births per month), the minimum monthly denominator will range from approximately 200 (repeat Caesarian section) to 7800 (group B Streptococcus screening). Thus, we expect to have sufficient sample sizes to ensure stable estimates.

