## Discussion

### Strengths and limitations

A major strength of our study is the use of a mixed methods approach to obtain more in-depth understanding of factors that influence use of an A&F system to improve performance. Additional strengths include the use of a theoretical framework (PARiHS) and a validated instrument (OR4KT) to guide data collection and analysis for objectives 2 (interviews) and 3 (provincial survey). We will have a large and inclusive sample size—all 94 maternal-newborn hospitals in Ontario for objectives 1 (ITS) and 3 (provincial survey), and therefore, we have the unique opportunity to see a wide variety of practice patterns and to examine use of the MND at a health system level, across diverse organizations and levels of care. We anticipate our project will provide important information to health-care funders and legislators, hospital administrators, and health-care providers. We will also use the findings from this collection of studies to support the development of a series of cluster randomized trials to test how to best to implement A&F in the future.

Study limitations include (1) exclusion of home births as the MND was customized for hospital birth performance issues; however, this group accounts for less than 2 % of all births in the province. Hospital births by midwives will be included; (2) any observed performance change could be due to factors other than the MND implementation; however, we will implement several strategies to allow us to quantitatively assess whether this may be the case; (3) a small number of hospitals will be excluded from the multivariable regression analysis due to low birth volumes; however, all remaining hospitals will be included in multivariable regression analyses to identify predictor variables; and (4) there is a risk of non-response bias in the provincial survey; however, BORN Ontario works within a network of all maternal-newborn care organizations in the province and has a well-established communication network established with health-care providers working within these settings, which will facilitate recruitment and data collection.

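### A null result in the two control outcomes is counted as support for the dashboard without regard to how precisely they are measured or how large the KPI change is

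*Protocol article*

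**What the plan says.** The Methods text of Objective 1 accepts that concurrent interventions threaten an interrupted time series and offers two checks. One uses control outcomes: "First, we will assess two non-equivalent outcomes measured in the same population over the same period of time". These are the cesarean rate in induced nulliparous women and electronic fetal monitoring in low-risk women at term. The reading of this check is stated: "a finding of no change in these variables will strengthen our ability to attribute any change in the KPIs to the MND". The other check is external: "Second, we will use data from two Canadian provinces (Nova Scotia and British Columbia) as a non-equivalent control group".

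The Analysis text sets the data as a "3-year pre-implementation period (November 2009–October 2012) and the 2-year post-implementation period (April 2013–March 2015", and adds: "We will exclude data from the 5–6 months between the pre- and post-implementation phases from the analysis". The model has separate intercepts and slopes before and after. For the KPIs, "The results of the segmented regression analysis of each KPI will be reported as level and trend changes after the intervention", with 95 % CIs. No model or report is described for the two control outcomes.

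The Sample size considerations argue from the number of time points and from KPI denominators: "the minimum monthly denominator will range from approximately 200 (repeat Caesarian section) to 7800 (group B Streptococcus screening". No denominator or detectable change is given for either control. Under Strengths and limitations, on causes other than the dashboard, the article says "we will implement several strategies to allow us to quantitatively assess whether this may be the case".

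**The concern.** The reasoning runs from a null result in the controls to stronger attribution of any KPI change. A null result supports that only if the controls could have shown a change of the size seen in the KPI. If a control is noisier than the KPI, a cause acting on both (data capture, case mix, general quality-improvement activity) can be clear in the KPI and invisible in the control. The imprecise null would then count for the dashboard, although the check was added to guard against exactly that error. The risk is greatest where the KPI series is precise and the shared change is small.

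**Working it through.** **The plan's own figure.** 36 + 24 = 60 time points, and 60 / 4 = 15 observations per coefficient, above the 10 that the article asks for. The figure reproduces. It guards against over-fitting and does not say what change can be detected.

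**Precision of a level change.** Assumptions: the controls get the same model as the KPIs; the gap is 5 months (November 2012 to March 2013); errors are independent with SD σ. Model: y = b0 + b1·t + b2·P + b3·P·(t − 42) + e, with t = 1–36 and 42–65, and P = 1 from month 42. Then SE(b2) = σ·√[(X′X)⁻¹]₃₃ = 0.571σ. With 56 df, t = 2.003, so the 95 % half-width is 2.003 × 0.571σ ≈ 1.14σ. With first-order autocorrelation of 0.2 or 0.4 it becomes 1.37σ or 1.65σ.

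Power for one series (noncentral t, two-sided 5 %, noncentrality = shift / 0.571σ):

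- 0.5 SD: 14 %
- 1 SD: 41 %
- 1.5 SD: 73 %
- 2 SD: 93 %
- 80 % power needs 1.63 SD

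These shift sizes are chosen for illustration. The article states no residual SD.

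**In percentage points.** σ = 100·√(p(1 − p)/n), binomial error only. The 7800 is from the article; every other input below is assumed.

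- KPI 5: n = 7800, p = 92 %, σ = 0.31
- Cesarean control: n = 800–1200, p = 25–35 %, σ = 1.25–1.69
- Fetal monitoring control: n = 4000, p = 60–75 %, σ = 0.68–0.77

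The article's inference refers to both controls, so the relevant event is that KPI 5 is detected and both controls are missed. Treating the three series as independent, its probability is the product:

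| Shared shift (points) | KPI 5 detected | Cesarean missed | Monitoring missed | KPI 5 detected, both missed |
|---|---|---|---|---|
| 0.5 | 80 % | 89–92 % | 76–80 % | 54–59 % |
| 1.0 | about 100 % | 72–82 % | 29–40 % | 21–33 % |
| 1.5 | about 100 % | 46–67 % | 4–9 % | 2–6 % |
| 2.0 | about 100 % | 21–47 % | below 1 % | at most 0.3 % |

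Example, upper end at 0.5 points: 0.799 × 0.920 × 0.801 = 0.59.

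**On the log-odds scale.** σ = 1/√(n·p(1 − p)): KPI 5 0.042, monitoring control 0.032–0.037, cesarean control 0.061–0.082. The assumed monitoring control is now more precise than KPI 5. For a shared shift of 0.05 the joint event is 0.54 × (0.70–0.82) × (0.24–0.35), or about 9–15 %. For 0.10 it is near zero.

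**At the other end, KPI 4.** With n ≈ 200 (article) and p = 11–40 % (assumed), σ = 2.21–3.46 points. The shift detected with 80 % power is 1.63σ, or 3.6–5.6 points. A shared shift of that size is found by the cesarean control with at least 95 % power and by the monitoring control almost always.

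**What a CI reading would show.** Suppose KPI 5 moves by 1 point and both control estimates are zero. The cesarean control's half-width is 1.14 × (1.25–1.69) = 1.4–1.9 points, which includes 1 point: inconclusive. The monitoring control's is 1.14 × (0.68–0.77) = 0.8–0.9 points, which excludes it: supportive.

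**The case against.** A reader might infer more: that because one series misses a 0.5-SD shift 86 % of the time, shared changes will usually be credited to the dashboard. The article does not support that. The 0.5 SD is an arbitrary size in units of an unstated SD. The KPIs run on the same model, so at equal precision a KPI shifted by 0.5 SD is itself detected only 14 % of the time. Detecting it while missing both controls then has probability 0.138 × 0.862² ≈ 10 %. A larger figure needs controls noisier than the KPI, and their denominators are not given. KPI 5 has the largest denominator and so is the least favorable example.

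The text can also be defended. It speaks of strengthening attribution, not proving it. It never equates non-significance with no change, and it is compatible with a CI reading. It adds two comparison provinces and concedes that other causes may explain a change. A margin may also sit in a fuller document that is not shown.

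Most of this stands, and the absence of a margin from a condensed article is not the point. What remains is an inference the article does state: a null in the controls strengthens attribution of any KPI change, whatever its size and however wide the controls' intervals. The comparison with the provinces is a separate check and does not repair this one.

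**Conclusion.** The concern holds in a limited form. The stated reading of the control outcomes ignores their precision and the size of the KPI change. With a level-change CI of about ±1.14 residual SDs, a null control can leave room for a small shared change.

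The frequency of false reassurance cannot be fixed from the article. Under the assumed sizes it is material for KPI 5 at shared shifts of about 1 percentage point or less, and small from 1.5 points upward. It is much lower on the log-odds scale and is not a concern for KPI 4. These figures rest on binomial error only, independent series and a common model; positive autocorrelation or extra-binomial variation would generally make the controls less precise. A general claim that undetected shared changes will be credited to the dashboard is not supported. The KPI estimates themselves are not affected.

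**What to change.** In the Methods text of Objective 1, replace the reliance on a null finding with a reading based on confidence intervals:

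- Report the level and trend change of each control outcome with its 95 % CI, from the same segmented model as the KPIs and on the same stated scale.
- Call the check supportive for a KPI only if the control's CI excludes a change as large as the KPI's. Otherwise call it inconclusive.
- A KPI-minus-control difference may be shown as an optional, descriptive result. It should not be the criterion, because it assumes that a shared cause moves unlike outcomes by the same amount on the chosen scale.

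The comparison with the two provinces stays as a separate check. The cost is a change of wording and no new data. The downside is that for some KPIs the check will be inconclusive where the present wording would call it supportive.
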